### Analysis strategy

The analysis will be per intent to treat. The mean and standard deviation shall be applied to the continuous variables, and percentages to the categorical variables. For comparison of two independent samples, the *t* test and analysis of variance will be applied for continuous variables and the chi-square test for categorical variables. In addition, nonparametric tests will also be applied for analysis. The efficacy for patients taking any pharmacologic medicine will be assessed using the method of last observation carried forward.

As mentioned above, the exploration analysis on core drug patterns will only be based on the effective patients in order to guarantee the efficacy of the explored core prescription. The patients’ syndrome and signs, CM patterns and the treatment effect shall be considered during the analysis. The core drug pattern can be concluded from the combination of high correlation and frequency. The core drug patterns must confirm to the CM theory and be accepted by the prestigious Chinese clinicians. The multi-dimension association rule and scale-free networks method will be applied to mine the core drug patterns and drug utilization rule of three Chinese clinicians [15,20-22]. In CM, the disease syndromes and signs, disease pattern and treatment are a dynamic procedure. The disease pattern varies with syndromes and signs. As a result, the treatment varies with the pattern of disease. So we not only explore the core drug patterns of different prestigious Chinese clinicians, but also mine the core drug patterns corresponding to different syndrome combinations and disease patterns.

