### Primary efficacy indicator

#### Total Sleep Time (TST)

In this study, the major indicator is the total sleep time (TST), which is assessed according to the sleep diary. All patients are required to record their sleeping information in detail every day. The sleep diary contains the following information: the time a patient goes to bed and gets out of bed; the time a patient thinks sleep onset occurs; the presumed cause, number, time, and length of any nighttime awakenings and activities during these moments; the name, dosage and time of any drugs used, including medication, sleep aids, caffeine and alcohol, and so forth; and activities happening 3 hours before bedtime, such as meditation, watching television, playing PC games, exercise, and so forth.

The efficacy can be confirmed only when improvement in TST is >0.5 hours and is considered statistically significant. Normally, the participants are not allowed to take any pharmacologic medicine used to treat insomnia. However, they are allowed to do so if they could not bear the bitterness brought about by insomnia. Under such circumstances, the dosage and the name of the medicine must be recorded carefully in sleep diaries.

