### Statistical methods

#### Sample size

The study is supposed to explore the daily clinical practice of three prestigious Chinese clinicians in primary insomnia treatment and to figure out the effective drug patterns prescribed by them. However, it is very difficult to estimate the sample size because of lack of a previous relevant study. To obtain expected results with a minimal sample size, a sequential design will be employed. The interim analysis will be conducted when the total number of patients having completed the study reaches 80 and 160 separately, for which we set up the early stopping criteria. The interim study can be treated as final if the difference in TST changes from baseline at 4 weeks between the CM and placebo groups is >0.5 hours and has statistical significance with *P* <0.05. When the early stopping criteria are met, the placebo group and the non-effective group will be dropped. The subsequent study will only focus on the effective group to explore the core drug patterns. If the number of effective patients is not sufficient to determine the core drug patterns, the recruitment procedure has to continue. The core drug pattern analysis shall be carried out every time the increment of new enrollment reaches 30 until the core drug patterns are obtained and kept constant.

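### The stated test of the primary endpoint is an unadjusted t test/ANOVA on change in total sleep time: valid at a single look, but less efficient than adjusting for washout-week sleep time

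*Protocol article*

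**What the plan says.** Under Total Sleep Time (TST), the primary endpoint is fixed: "the major indicator is the total sleep time (TST), which is assessed according to the sleep diary".

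Under Sample size, a look may end the study when "the difference in TST changes from baseline at 4 weeks between the CM and placebo groups is >0.5 hours", provided that this difference also "has statistical significance with *P* <0.05". Meeting the rule leads to the placebo group and the non-effective group being dropped. The timing is set there too: "The interim analysis will be conducted when the total number of patients having completed the study reaches 80 and 160 separately".

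The Analysis strategy section gives one rule for every continuous variable, the *t* "test and analysis of variance will be applied for continuous variables and the chi-square test for categorical variables", and adds that "nonparametric tests will also be applied for analysis". The article names no baseline covariate, ANCOVA, regression or mixed model, and no stratified randomisation.

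Table 1 schedules the sleep diary at screening, in the washout week (week 0) and in weeks 1 to 4. A pre-randomisation TST is therefore planned for every patient.

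**The concern.** A change score subtracts the whole of a patient's baseline value. Week-4 TST will generally follow baseline with a slope below 1, so full subtraction takes off too much. An arm that by chance starts with shorter sleep then appears to gain more than it did. ANCOVA estimates the slope from the data and removes that part.

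This matters because a fixed 0.5 h threshold and a P value, first applied at 80 completers, decide whether the placebo comparison ends and which arms continue. The Sample size section also says that the sequential design is meant to keep the sample small, and discarding precision that the diary already supplies works against that aim.

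**Working it through.** The article states no power, SD, correlation or sample-size calculation, so there is no figure to reproduce. What follows uses its design numbers with labelled assumptions.

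**Inputs from the article.** Equal allocation to four groups (Randomization); looks at 80 and 160 completers (Sample size); maximum 300 (Abstract); threshold 0.5 h. Per group: 80/4 = 20, 160/4 = 40, 300/4 = 75.

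**Assumed inputs.** TST SD s of 1.0 to 1.25 h; baseline to week-4 correlation ρ of 0.3, 0.5 or 0.7; equal SDs at the two times unless stated; two-sided 0.05.

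**1. Direction.** With baseline SD s₀ and week-4 SD s₁:
- Var(change) = s₀² + s₁² − 2ρs₀s₁
- Var(ANCOVA) = s₁²(1 − ρ²)
- The difference is (s₀ − ρs₁)², which is never negative.

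Estimating the slope adds a small cost: with 20 per group the ANCOVA variance rises by about 1/36. With equal SDs this outweighs the gain only when ρ exceeds about 0.95.

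**2. Size with equal SDs.** The ratio ANCOVA/change is s²(1 − ρ²) / 2s²(1 − ρ) = (1 + ρ)/2.

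| ρ | Ratio | Variance saved | Ratio simulated, 20 per group | Power at a true 0.5 h, s = 1.0 h (simulated): change → ANCOVA |
|---|---|---|---|---|
| 0.3 | 0.65 | 35% | 0.66 | 0.26 → 0.35 |
| 0.5 | 0.75 | 25% | 0.77 | 0.34 → 0.42 |
| 0.7 | 0.85 | 15% | 0.87 | 0.51 → 0.57 |

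**3. Size with unequal SDs.** Take s₁ = 1.4 s₀, as an illustration:
- ρ = 0.5: 1.96 × 0.75 / (1 + 1.96 − 1.4) = 1.47/1.56 = 0.94
- ρ = 0.7: 1.96 × 0.51 / (1 + 1.96 − 1.96) = 0.9996/1 = 1.00

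The gain is then small or nil.

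**4. Chance imbalance.** The SD of the baseline difference between two groups of n is s√(2/n). With equal SDs the change score carries −(1 − ρ) times that imbalance. At ρ = 0.5:

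| Comparison | SD of imbalance, s = 1.0 / 1.25 h | Shift for a one-SD imbalance |
|---|---|---|
| 20 v 20 (first look) | 0.32 / 0.40 h | 0.16 / 0.20 h |
| 60 v 20 (first look, CM pooled) | 0.26 / 0.32 h | 0.13 / 0.16 h |
| 40 v 40 (second look) | 0.22 / 0.28 h | 0.11 / 0.14 h |
| 75 v 75 (maximum) | 0.16 / 0.20 h | 0.08 / 0.10 h |

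The 60 v 20 row uses s√(1/60 + 1/20). At ρ = 0.7 the first-row shift falls to 0.3 × 0.32 = 0.09 h and 0.3 × 0.40 = 0.12 h.

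**5. Effect on the rule.** Simulation with no true effect, s = 1.0 h, ρ = 0.5 and 20 per group:
- Over all randomisations both tests reject at about 5%.
- The treated arm starts more than 0.3 SD lower in about 17% of trials. In those trials the change score shows a mean spurious gain of about 0.23 h, and ANCOVA about zero.
- In the same trials the full rule (>0.5 h and P<0.05) is met in about 9% with the change score and 2.5% with ANCOVA. A shorter run of 20,000 trials gave 7.5% and 1.7%.

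**The case against.** The strongest reply is that nothing here is wrong. Under randomisation a *t* test on change is a standard, unbiased analysis with the right error rate at a single look, and covariates are often settled in an analysis plan that is not shown. The trial also calls itself exploratory and plans a further randomised trial.

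The first part stands: the issue is efficiency and conditional error, not validity. The second does not dispose of the point, because the article states an unadjusted method rather than leaving the method open. It is true that tying the general rule for continuous variables to the TST stopping rule is an inference, since Analysis strategy does not name TST. But no other test of the primary endpoint is offered.

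A reader might infer that baseline imbalance goes uncorrected and is by itself nearly as large as the 0.5 h threshold. That is not supported. The change score does use baseline, and the 0.32 to 0.40 h is the raw imbalance; only (1 − ρ) of it reaches the estimate. The rule also demands P<0.05, and that test's standard error already allows for chance imbalance.

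A reader might also infer that decisions always rest on 20 per group, or that ANCOVA always wins. Twenty applies only at the first look with clinicians compared singly, and the article does not say whether the CM groups are compared singly or pooled. In small samples with a slope close to 1, the change score can be marginally more precise.

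**Conclusion.** The point holds as a recommended improvement at almost no cost. It is not an error that invalidates the trial. The stated analysis is valid at a single look but gives up precision that the planned diary data would supply.

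If the SDs at baseline and week 4 are equal, the loss is about 35%, 25% or 15% of the variance for a correlation of 0.3, 0.5 or 0.7. It shrinks if sleep time becomes more variable by week 4, to almost nothing at an SD ratio of 1.4 and correlation 0.7. At the first look, the 0.16 to 0.20 h shift for a one-SD imbalance is about a third of the threshold or somewhat more, and it is smaller at later looks or with pooled CM groups. The direction follows from the algebra, apart from the small slope-estimation cost. The sizes rest on an SD and a correlation that the article does not give.

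**What to change.** Before the first look, name as the primary analysis an ANCOVA of week-4 diary TST on treatment group, with washout-week (week 0) diary TST as covariate. Apply the >0.5 h and P<0.05 rule to the adjusted difference at every look, and say that this replaces the general *t* test/ANOVA rule for the primary endpoint. If an existing analysis plan already does this, the two documents need only be aligned.

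The cost is a change of wording and one degree of freedom for the slope. No new data, visits or patients are required.

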**Figure 1 F1:**
[figure not shown]
Trial design.

**Table 1 T1:** Calendar summary

**Period**	**Screening**	**Washout**	**Treatment**				**Follow-up**
**Week(W)**	**-1 W**	**0 W**	**1 W**	**2 W**	**3 W**	**4 W**	**4th week after the end of treatment**
Inclusion and exclusion criteria	×						
Informed consent	×						
Demography	×						
Past Medical history & treatment history	×						
Spiegel Scale	×	×					
Self-rating Anxiety Scale	×	×				×	
Beck Depression Inventory	×	×				×	
http://Pittsburgh Sleep Quality Index	×	×	×	×	×	×	×
CM syndromes and signs	×	×	×	×	×	×	×
Sleep diary	×	×	×	×	×	×	
Prescription (include every herb and dose)			×	×	×	×	
Vital signs	×	×	×	×	×	×	
Adver event		×	×	×	×	×	

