### Eligibility criteria

#### Inclusion criteria and exclusion criteria

Patients are eligible to participate if they are aged between 18 and 65 years, and meet the definition of insomnia from the *Diagnostic and Statistical Manual of Mental Disorders*, Fourth Edition, Text Revision, with Spiegel scale >18. It is imperative that patients should read and sign an informed consent form to participate in the trial.

The following exclusion criteria are observed: total sleep time <2 hours, secondary insomnia, Self-rating Anxiety Scale score >60, Beck Depression Inventory score <8, complicated with hypertension, diabetes, stroke, and coronary heart disease, having drug abuse history, pregnancy or preparing for pregnancy, and participating in another clinical trial at the same time.

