### Secondary efficacy indicators

The secondary efficacy indicators include sleep onset latency, wake time after sleep onset, sleep efficiency, Pittsburgh sleep quality index (PSQI) and CM symptoms and signs. Sleep onset latency, wake time after sleep onset and sleep efficiency are obtained from the sleep diary. The Chinese-version PSQI is employed to measure the quality of sleep. The PSQI is a self-rated questionnaire used to assess sleep quality and disturbances over a 1-month time interval. Nineteen individual items generate seven component scores: subjective sleep quality, sleep latency, sleep duration, habitual sleep efficiency, sleep disturbances, use of sleeping medication, and daytime dysfunction.

Many studies have demonstrated that the Chinese-version PSQI is a sensitive, reliable, and valid tool to assess the quality of sleep [18,19]. In addition, CM symptoms and signs will be assessed. The main symptoms and signs include headache, dizziness, spontaneous sweating, night sweating, dreaminess, amnesia, anorexia, lassitude of spirit and lack of strength, oppression in the chest, daytime sleepiness, irritability, palpitations, epigastric fullness, tinnitus, thirst, bitter taste in the mouth, abundant sputum, yellow urine, dry stool, sloppy stool, pulse condition, and tongue manifestation.

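### The one test named for categorical outcomes makes no use of whether a Chinese medicine (CM) symptom was present at washout; if symptoms are analysed as present or absent, the test is valid but loses power

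*Protocol article*

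**What the plan says.** The Analysis strategy section of the protocol article sets out one general scheme: t test and analysis of variance for continuous variables, "and the chi-square test for categorical variables", all framed as comparisons of two independent samples. It adds "In addition, nonparametric tests will also be applied for analysis", without naming them, and states "The analysis will be per intent to treat". No baseline term, stratum or baseline-defined subset appears for any categorical variable.

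The section on secondary efficacy indicators ends its list with "sleep efficiency, Pittsburgh sleep quality index (PSQI) and CM symptoms and signs". It then names 20 symptoms plus pulse condition and tongue manifestation, beginning "The main symptoms and signs include headache, dizziness, spontaneous sweating, night sweating, dreaminess, amnesia, anorexia". It does not say whether each item is recorded as present or absent, graded, or summed to a score.

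Entry rests on age and a DSM-IV-TR diagnosis, "Fourth Edition, Text Revision, with Spiegel scale >18". None of the listed symptoms is required. Table 1 has a row for "CM syndromes and signs" marked at screening, washout, weeks 1 to 4 and follow-up, so a value before treatment exists for every patient who attends those visits.

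**The concern.** Because no CM symptom is required at entry, any one of them will be absent in some patients at washout. Dry stool and sloppy stool are both listed, and few patients will have both. A chi-square test of presence at week 4 puts two different kinds of patient in the symptom-free cell: those whose symptom resolved and those who never had it. The second kind says little about whether treatment clears the symptom and shrinks the difference between groups. Washout status is also likely to be the strongest predictor of week-4 status, and leaving it out puts the variation it explains into the error term.

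What is at stake is the chance of detecting a real effect on a named secondary efficacy indicator, especially for the less common symptoms.

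**Working it through.** **No plan figure to reproduce.** The article gives no power, effect size, symptom prevalence or persistence rate, and the maximum of 300 comes without a calculation.

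**Inputs from the article.** Four equal groups. The Abstract's maximum of 300 gives 300/4 = 75 per group; the interim looks at 80 and 160 completers give 20 and 40.

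**Assumed inputs.** Two-sided 5% (the article states 0.05 for total sleep time only); symptom scored present or absent; persistence to week 4 among patients with the symptom at washout p0 = 0.80 on placebo and p1 = 0.50 on CM; new onset e = 0.05 in both groups; washout prevalence b varied; no dropout; one CM group against placebo.

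**Plain test, all patients.** The week-4 rate in a group is q = b·p + (1 − b)·e. At b = 0.30:
- placebo q0 = 0.30·0.80 + 0.70·0.05 = 0.275
- CM q1 = 0.30·0.50 + 0.70·0.05 = 0.185
- difference d = 0.090, mean rate 0.230

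Power ≈ Φ{[d√n − 1.96√(2·0.230·0.770)] / √(0.275·0.725 + 0.185·0.815)} = Φ{[0.779 − 1.166] / 0.592} = Φ(−0.65) ≈ 26%.

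**Test stratified by washout status, all patients.** The difference is the same, b(p0 − p1) = 0.30·0.30 = 0.090, but only within-stratum variance counts:
- under the null: 0.30·2·0.65·0.35 + 0.70·2·0.05·0.95 = 0.1365 + 0.0665 = 0.203
- under the alternative: 0.30·(0.80·0.20 + 0.50·0.50) + 0.0665 = 0.123 + 0.0665 = 0.1895

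Power ≈ Φ{[0.779 − 1.96√0.203] / √0.1895} = Φ{[0.779 − 0.883] / 0.435} = Φ(−0.24) ≈ 41%.

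The plain test uses 2·0.230·0.770 = 0.354 where the stratified test uses 0.203. That gap is the whole loss.

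**Simulated power, 75 per group** (chi-square, Mantel-Haenszel, and chi-square in the washout-positive subset):

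| Prevalence at washout | Plain | Stratified | Washout-positive subset |
|---|---|---|---|
| 20% | 17% | 25% | 42% |
| 30% | 26% | 41% | 57% |
| 50% | 49% | 70% | 79% |
| 70% | 75% | 88% | 91% |
| 90% | 94% | 96% | 97% |

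Type I error was about 5% for all three. At 40 per group and 30% prevalence the figures are 16%, 24% and about 35%.

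**Sensitivity.** With persistence 0.7 vs 0.4 and e = 0.05 at 75 per group, plain versus stratified power is 17.5% vs 23.1% at 20% prevalence, 27.9% vs 38.7% at 30%, 51.8% vs 67.3% at 50% and 91.9% vs 94.3% at 90%. Over a wider grid (prevalence 20% to 90%, four persistence pairs, new onset 0 to 10%) the plain test keeps between 0.48 and 0.99 of the stratified test's power, and between 0.36 and 0.98 of the subset test's. It was the weaker test in every equal-allocation scenario.

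**The case against.** The strongest reply is that the article never says CM symptoms will be compared by a plain chi-square test at week 4. The sentence is generic. If items are graded or summed, the t test or the unnamed nonparametric tests would apply. A comparison of resolution among washout-positive patients could itself be run as a chi-square test. Endpoint coding and baseline handling may sit in a full protocol or analysis plan that is not shown. This stands, and it makes the point conditional. What remains is that the article does name a method for categorical variables, that the method as named uses no baseline information, and that a better one is available from data already collected.

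A reader might infer that power is roughly halved. That holds only against the washout-positive subset, and only at about 20% to 30% prevalence (for example 26% against 57%). Against the stratified test, which keeps everyone, the loss is smaller, and at 90% prevalence it nearly disappears. The article gives no prevalence to choose between these.

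A reader might also infer that chance imbalance at washout biases the result. It does not: with randomized allocation the plain test holds its 5% error rate, and imbalance is part of the noise that rate already covers.

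The subset has the highest power, but it should not lead. It departs from the stated intent-to-treat analysis and cannot see symptoms that begin on treatment. At 20 per group and 30% prevalence it leaves about 20·0.30 = 6 patients per group.

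**Conclusion.** The point holds as a conditional remark on efficiency. If CM symptoms are analysed as present or absent with the test named, the analysis is valid but weaker than it need be. At 75 per group and the assumed 80% vs 50% persistence with 5% new onset, stratifying by washout status adds about 8 percentage points of power at 20% prevalence (25 − 17), 15 at 30% (41 − 26), 21 at 50% (70 − 49) and 2 at 90% (96 − 94). All these rates are assumptions; only the group size comes from the article.

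The consequence is limited. The indicator is secondary, the efficacy criterion for early stopping rests on total sleep time alone, and the authors describe the study as exploratory. At the first interim look every method has low power for a minority symptom. This is a worthwhile refinement and no threat to the trial's main conclusion.

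**What to change.** State how each CM symptom is scored. For each one, compare groups in all randomized patients at week 4 with a Mantel-Haenszel test stratified by the washout-visit value, or with a logistic model adjusted for that value (ordinal if the symptom is graded). As a supportive analysis, report resolution among patients who had the symptom at washout. Report pulse and tongue descriptively, because no direction of benefit is stated for a change of category.

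The cost is plan wording and slightly more analysis work; the washout values are already scheduled. The supportive subset will be small for uncommon symptoms, which should be said when it is reported.

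### Carrying the last observation forward for medicine takers replaces observed week-4 sleep times, is inconsistent with the declared intent-to-treat analysis, and can bias the comparison either way if rescue use differs by group

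*Protocol article*

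**What the plan says.** All of this is in the protocol article.

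- Analysis strategy declares "The analysis will be per intent to treat". The same paragraph ends with "The efficacy for patients taking any pharmacologic medicine will be assessed using the method of last observation carried forward".
- The section on total sleep time (TST) sets the background: "Normally, the participants are not allowed to take any pharmacologic medicine used to treat insomnia". An exception follows: "However, they are allowed to do so if they could not bear the bitterness brought about by insomnia". It then requires that "the dosage and the name of the medicine must be recorded carefully in sleep diaries". No withdrawal after rescue is stated.
- The same section says "All patients are required to record their sleeping information in detail every day", and Table 1 schedules the diary at every week through week 4 of treatment.
- Sample size ties efficacy and early stopping to week 4. The criterion is that "the difference in TST changes from baseline at 4 weeks between the CM and placebo groups is >0.5 hours", together with P below 0.05.

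The article does not say which observation is carried forward, nor what effect the rule is meant to estimate.

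**The concern.** Carrying forward is a device for missing values. Here the trigger is taking a medicine, not a missing diary. For a patient who takes rescue and keeps the diary, the rule has an effect only if a recorded week-4 TST is set aside for an older one. That sits badly with an intent-to-treat analysis, which uses outcomes as they occurred after randomisation.

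One might defend the rule as an attempt to estimate the effect without rescue. It then assumes that TST would have stayed at its last value before rescue. If sleep improves over the four weeks, that removes later improvement from whichever group uses more rescue, and the difference shifts.

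At stake is the week-4 comparison that decides whether the trial stops and which groups are dropped. The core drug patterns are mined only from effective patients. If effectiveness is judged on the carried-forward TST, the rule also affects who enters that analysis.

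There is a smaller mismatch of wording. The TST section speaks of medicine for insomnia, while the analysis rule has no such limit.

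**Working it through.** The article states no figure here that could be reproduced. From the article: the criterion of more than 0.5 h with P below 0.05 at week 4; four equal groups; looks at 80 and 160 completers and a maximum of 300, hence 80/4 = 20 and 300/4 = 75 per group at the first look and the maximum. Everything else below is assumed.

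**Step 1: does the rule act on observed data?** Rescue is allowed, is recorded in the diary, and is not linked to withdrawal. The diary is daily through week 4. So rescue users normally have a week-4 value, and the rule replaces it.

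**Step 2: closed form.** Let rP and rC be the rescue proportions on placebo and Chinese medicine (CM), and GP and GC the gain between the carried-forward week and week 4. If rescue users are a random subset, the shift relative to no rescue is

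shift = rP × GP − rC × GC.

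Assume no drug effect, a common gain of 0.20, 0.35, 0.45 and 0.50 h at weeks 1 to 4, and rescue 20 or 30 percentage points commoner on placebo:

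- Rescue from week 1 (baseline carried): G = 0.50; 0.20 × 0.50 = 0.10 h, 0.30 × 0.50 = 0.15 h.
- From week 2 (week 1 carried): G = 0.50 − 0.20 = 0.30; 0.06 h, 0.09 h.
- From week 3 (week 2 carried): G = 0.50 − 0.35 = 0.15; 0.03 h, 0.045 h.

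The range of 0.03 to 0.15 h is 6% to 30% of 0.5 h. Equal rates and equal gains give zero.

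**Step 3: simulation.** 400 runs per scenario, 75 per group. Between-patient SD 1.0 h and week-to-week SD 0.7 h, so the SD of change is √(2 × 0.7²) = 0.99 h. Placebo gains 0.5 h linearly over four weeks; CM gains 0.5 h (no effect) or 1.0 h (0.5 h effect). Rescue starts in week 3, adds 0.75 h, and week 2 is carried forward. Rescue users are either random or those with the worst early change. Mean week-4 differences in hours, CM minus placebo (random / worst early change):

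| True effect | Rescue placebo/CM | No rescue | All observed diaries | Carried forward |
|---|---|---|---|---|
| 0 | 20%/20% | −0.01 / −0.01 | −0.01 / −0.01 | −0.01 / −0.01 |
| 0 | 30%/10% | −0.01 / 0.00 | −0.15 / −0.14 | +0.03 / +0.10 |
| 0 | 40%/10% | −0.01 / 0.00 | −0.23 / −0.22 | +0.06 / +0.12 |
| 0 | 10%/30% | −0.01 / 0.00 | +0.14 / +0.14 | −0.05 / −0.10 |
| 0.5 | 20%/20% | 0.50 / 0.48 | 0.50 / 0.48 | 0.45 / 0.43 |
| 0.5 | 30%/10% | 0.49 / 0.51 | 0.35 / 0.37 | 0.52 / 0.57 |
| 0.5 | 40%/10% | 0.51 / 0.50 | 0.29 / 0.28 | 0.56 / 0.60 |
| 0.5 | 10%/30% | 0.49 / 0.50 | 0.63 / 0.64 | 0.37 / 0.33 |

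The closed form agrees for random users. With no effect and 30%/10%, it gives 0.3 × 0.25 − 0.1 × 0.25 = +0.05 h; the simulated shift is 0.034 − (−0.012) = +0.046 h. With a 0.5 h effect and 20%/20%, it gives 0.2 × 0.25 − 0.2 × 0.50 = −0.05 h; simulated, 0.452 − 0.498 = −0.046 h.

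**Step 4: false positives.** With no effect, significant results favouring CM occurred in 4.0% (random) and 6.5% (worst early change) of runs at 30%/10%, and in 6.2% and 9.8% at 40%/10%, against a nominal 2.5%. With 400 runs the simulation error at 2.5% is √(0.025 × 0.975/400) = 0.8 points, so 4.0% alone is weak evidence and the other three are clear. These rates are for P below 0.05 only, without the additional requirement of more than 0.5 h.

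**The case against.** The strongest defence is that the rule has an evident purpose: a hypnotic's benefit should not be credited to the assigned granules. For that purpose, using all observed diaries is not neutral. With a 0.5 h effect and the worst early responders rescued, observed diaries miss the no-rescue value by 0.37 − 0.51 = −0.14 h at 30%/10%, and carrying forward by 0.57 − 0.51 = +0.06 h. At 40%/10% the errors are 0.28 − 0.50 = −0.22 h and 0.60 − 0.50 = +0.10 h. This stands: for the drug-alone effect, observed diaries are further off in these scenarios. It is a reason to name the target effect and report both estimates. It does not rescue the rule, which misses both targets here.

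The sizes also rest on assumed inputs. Every patient takes placebo in the washout week, so part of any placebo response may precede baseline, which would shrink the gain and the bias in proportion. The upper figures need all rescue to start in week 1. The study calls itself exploratory, plans a further trial, and requires both conditions of its criterion, so a shift of this size cannot meet the criterion unaided. It can still add to chance or to a real but smaller effect.

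A reader might infer more than the text supports:

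- That the rule flatly contradicts intent to treat. It does not: nobody is excluded or moved from the assigned group. The inconsistency lies in replacing observed outcomes.
- That a single dose in week 1 freezes a patient at baseline. The article does not say which observation is carried forward, and with a nightly diary, replacing only medicated nights is also possible.
- That unrelated drugs trigger the rule. Read literally they do, but the phrase may simply be a shortening of the one in the TST section.

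**Conclusion.** The point holds in this form. The rule replaces observed week-4 TST because of a post-randomisation event, which is inconsistent with the declared intent-to-treat analysis, and it does not reliably estimate the effect without rescue.

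With no true effect and rescue 20 to 30 points commoner on placebo, the assumed time course gives a bias towards CM of about 0.03 to 0.15 h. More rescue on CM reverses the sign. Identical treatments with equal rescue use give none; with a real effect, equal rates can still shrink the estimate (0.43 to 0.45 h in the 20%/20% scenarios, against 0.48 to 0.50 h without rescue). Where the true effect is near 0.5 h, the choice of rule can put the estimate on either side of the criterion.

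It would be natural to conclude that the rule always manufactures an advantage for CM. The article gives no rescue rates, so neither the direction nor the size is known in advance.

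**What to change.** Drop last observation carried forward.

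- **Primary analysis.** Weekly mean diary TST at weeks 1 to 4 in a mixed model for repeated measures, with treatment, week, treatment-by-week and baseline TST. Include all observed weeks regardless of rescue, with the week-4 contrast as the result. This matches the declared intent to treat.
- **Supporting analysis for the effect without rescue.** Set TST after recorded insomnia medication, or on nights with it, to missing (choosing one in advance), and use the same model or multiple imputation. State the missing-at-random assumption.
- **Reporting.** Give rescue use by group, and name the target effect beside each estimate.
- **Wording.** Reconcile the scope of medicine in the analysis rule with that in the TST section.

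The cost is a change of wording and analysis programs. Daily sleep and the name, dosage and time of drugs are already in the diary, and nothing in patient management changes. The downside is real: if rescue is commoner on placebo, the primary estimate can be clearly smaller than the drug-alone effect, about 0.28 to 0.37 h against 0.5 h in the assumed scenarios. Both estimates should therefore be reported.
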